**Methods:**

YLH (N=220) who are not virally suppressed will be identified at homeless shelters, health clinics, and gay-identified community-based organizations in Los Angeles, CA, and New Orleans, LA. Informed consent will be obtained from all participants. YLH will be randomly assigned to one of two study conditions: Enhanced Standard Care, which includes standard clinical care plus an automated messaging and monitoring intervention (AMMI), or an Enhanced Stepped Care, which includes three levels of intervention (AMMI, Peer Support via social media plus AMMI, or Coaching plus Peer Support and AMMI). The primary outcome is viral suppression of HIV, and YLH will be assessed at 4-month intervals for 24 months. For the Enhanced Stepped Care intervention group, those who do not achieve viral suppression (via blood draw, viral load<200 copies/mL) at any 4-month assessment will “step up” to the next level of intervention. Secondary outcomes will be retention in care, antiretroviral therapy adherence, alcohol use, substance use, sexual behavior, and mental health symptoms.

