### Recruitment Procedures

To identify eligible participants, youth in high-risk settings will be asked to complete a brief screening and rapid HIV test. All screenings are done face-to-face with a study team member from our Recruitment, Engagement, and Retention Center. Older youths (aged 15-24 years) will provide oral consent for the screening, and younger youths (aged 12-14 years) will provide written consent for the screening to ensure that they understand the screening process. Next, all youths aged 12-24 years whose judgment does not appear to be impaired from a disability or substance use will be asked to give written informed consent to complete the screening. Interviewers are trained to assess for problems with cognition, and additional screening questions will be asked if any concerns are identified. To qualify as “eligible” for recruitment, youths must test seropositive on a rapid HIV test and be virally unsuppressed. Based on these screening criteria, eligible youths will be invited to complete the voluntary informed consent (we have a waiver of parental consent for minors). YHL will be randomized to the intervention conditions via the CommCare system (see next section) after viral load results are obtained and entered, which typically takes several days.

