### Description of the Intervention

As shown in Figure 1, the Enhanced Stepped Care condition has three levels of intervention: Level 1, Enhanced Standard Care plus AMMI; Level 2, online peer support via social media plus AMMI plus Enhanced Standard Care; and Level 3, coaching plus online peer support via social media and AMMI plus Enhanced Standard Care. If YLH fail to be virally suppressed (based on analyses of viral load in the blood stream at 4-month intervals), YLH in the Enhanced Stepped Care condition will be provided the next level of intervention in addition to the other levels of care to which they were previously assigned. Note that these interventions overlap with our team’s other study of HIV-negative youths and are also described in Swendeman et al [49]. To assess dose of the interventions, we will examine the number of responses to the AMMI surveys (Level 1), the number of peer support posts and logins (Level 2), and the number of coaching sessions (Level 3).

#### Level 1

Level 1 of the Enhanced Stepped Care model is Enhanced Care plus AMMI. As this is not a medication treatment study, YLH are treated in the community using best practices that are consistent with available treatment guidelines for providers. However, given that YLH have failed to achieve viral suppression with the existing services available to them, we are enhancing standard care by adding an additional component. Thus, Enhanced Care includes existing services received by YHL from health care providers and other agencies as well as daily text messages. Messages for this study focus on five areas: wellness, health care, medication reminders, drug use, and sexual health. We have tailored and adapted preexisting libraries of theoretically based text messages that have been found to be successful in other RCTs with similar populations [80-83], with messages tailored for two different groups—GBTY and non-GBTY. Messages include a focus on empowering YLH (ie, “Don't rely on other people, take your health seriously,” and “When you take your meds regularly, you’re in control”) as well as providing health-related facts (“Meds keep HIV in check” and “Syphilis can increase your viral load”). The goal of AMMI is to target the areas that can impact adherence to ART that will translate into increased rates of viral suppression.

#### Level 2

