### Data Analyses

#### Aim 1

Intent-to-treat analyses will be used to compare viral suppression as our primary outcome and secondary outcomes between YLH randomized to the Enhanced Stepped Care or Enhanced Standard Care conditions. Comparisons of the same outcomes will also be made between steps in the Enhanced Stepped Care condition as exploratory analyses; the study is only powered for comparisons between study arms. Multilevel models (MLM [99]) will be used to model correlations between repeated observations on the same YLH in order to properly estimate standard errors. Generalized linear MLM will be fit to discrete outcomes such as the binary outcome for viral suppression. MLM fit to the primary outcome for viral suppression will be parameterized to test for the average of viral suppression differences over the follow-up period between study arms (ie, time-averaged effects). This parameterization will be used because all participants are virally unsuppressed at baseline based on eligibility criteria. Secondary outcome levels can differ across study arms; a more standard parameterization that allows for baseline and slope differences over time will be used. We anticipate that randomization will balance out sociodemographic and other important background characteristics across study arms. If characteristics are found to differ across study arms, they will be included as adjustment covariates in MLM. More sophisticated adjustment methods such as propensity scores will be implemented as needed [100]. Data will also be checked for missing data patterns. Appropriate statistical techniques such as multiple imputation will be applied [98,101].

#### Aim 2

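### Secondary outcomes: estimating a baseline arm difference that randomisation sets to zero in expectation gives away precision on the slope difference

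*Protocol article*

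**What the plan says.** The protocol article, Data Analyses, Aim 1, treats the two classes of outcome differently.

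- **Primary outcome.** The multilevel model "will be parameterized to test for the average of viral suppression differences over the follow-up period between study arms". The reason given is that everyone is unsuppressed at baseline by eligibility.
- **Secondary outcomes.** The article says that "Secondary outcome levels can differ across study arms", and therefore "a more standard parameterization that allows for baseline and slope differences over time will be used".
- **Randomisation.** The same paragraph states: "We anticipate that randomization will balance out sociodemographic and other important background characteristics across study arms". Recruitment Procedures places allocation "after viral load results are obtained and entered, which typically takes several days".
- **Care at entry.** The abstract gives the control arm standard clinical care plus the messaging intervention (AMMI). Description of the Intervention defines the entry level of the stepped arm as "Level 1, Enhanced Standard Care plus AMMI", which is the same package. The stepped arm moves up only for "those who do not achieve viral suppression (via blood draw, viral load<200 copies/mL) at any 4-month assessment".
- **Timing.** Sample Size Calculations leaves the first follow-up out of the primary comparison and uses five time points, that is, months 8, 12, 16, 20 and 24.

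**The concern.** That secondary outcomes vary at baseline is a reason to use the baseline measurement. It is not a reason to estimate an arm effect there. Under individual randomisation any baseline difference between arms is chance, and both arms then receive the same care until the month-4 result. A model with its own baseline difference for each arm discards this knowledge, and the slope difference, estimated jointly with the baseline difference, becomes less precise.

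Aim 1 includes improvement in secondary outcomes, and Aim 3 puts differences in them into cost-effectiveness ratios. Both would rest on wider intervals than the same data can give. A second, weaker question is whether a slope starting at month 0 suits an intervention whose arms cannot diverge before month 4.

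**Working it through.** **Inputs.** Visits at months 0, 4, …, 24 (Follow-Up Assessments), coded t = 0 to 6. 88 analysed per arm, compound symmetry and correlation ρ of .1 to .3 (Sample Size Calculations, for viral suppression). The protocol gives no correlation for secondary outcomes, so ρ = .5 and .7 are assumptions. Also assumed: a continuous outcome with SD 1, complete visits and a linear slope.

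**The plan's own figure.** The protocol states no power for secondary outcomes. Its primary figure is a detectable difference of 9 to 13 points. At ρ = .3 the effective number per arm is 88 × 5 / (1 + 4 × .3) = 200. A continuity-corrected two-proportion test then gives 9.1 and 12.8 points for control rates of 6% and 20% (8.5 and 12.3 without the correction). The figure reproduces at ρ = .3, so the design inputs are read correctly.

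**Step 1: variance of the slope difference.** Let n be the number per arm.

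- Free baseline: Var = 2(1−ρ) / (n × Σ(t−3)²), with Σ(t−3)² = 28.
- Baseline difference fixed at zero: Var = 2(1−ρ) / (n × B), with B = Σt² − ρ(Σt)²/(1+6ρ) = 91 − 441ρ/(1+6ρ).
- Inflation from leaving the baseline free: B/28. It does not depend on n.

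| ρ | B | B/28 | 88 per arm acts like 88 × 28/B |
|---|---|---|---|
| .1 | 63.44 | 2.27 | 39 |
| .2 | 50.91 | 1.82 | 48 |
| .3 | 43.75 | 1.56 | 56 |
| .5 (assumed) | 35.88 | 1.28 | 69 |
| .7 (assumed) | 31.63 | 1.13 | 78 |

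On the month-24 scale the standard error is 0.162 free against 0.108 constrained at ρ = .1, and 0.143 against 0.114 at ρ = .3. An assumed random-slope variance of 0.1 to 0.3 lowers the factor to 1.8–2.1 at ρ = .1 and 1.4–1.5 at ρ = .3.

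**Step 2: the months 8–24 average as comparator.** With a common baseline and categorical visits, its variance is (2/n)[(1+4ρ)/5 − ρ²] when month 4 is free. It is (2/n)[(1+4ρ)/5 − 2ρ²/(1+ρ)] when the arms are also held equal at month 4. Set this contrast to 80% power (noncentrality 1.960 + 0.842 = 2.802) and find the power of the slope tests for the same effect.

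*Constant effect from month 8.* The free-baseline slope picks up Σ(t−3)d/28 = 5/28 of the effect per visit. At ρ = .3, month 4 free, its noncentrality is 2.802 × [5/√(28 × .7)] × √.35 = 1.87, so power is Φ(1.87 − 1.96) ≈ 47%.

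*Effect growing linearly from month 4 to month 24.* Σ(t−3)d is again 5, but the months 8–24 average is only 0.6 of the final effect, so each noncentrality is divided by 0.6.

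| Effect shape and test (average set at 80%) | ρ .1 | ρ .3 | ρ .5 |
|---|---|---|---|
| Constant from month 8, free-baseline slope, month 4 free | 31% | 47% | 60% |
| Same, arms also held equal at month 4 | 30% | 41% | 49% |
| Constant from month 8, common-baseline slope, month 4 free | 74% | 75% | 77% |
| Linear from month 4, free-baseline slope, month 4 free | 68% | 88% | 96% |
| Linear from month 4, common-baseline slope, month 4 free | 90% | 95% | 98% |

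The common baseline raises the power of the slope test under both shapes. Whether the months 8–24 average beats the free-baseline slope depends on the shape.

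**The case against.** The strongest points on the other side are these.

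- **The model is conventional and valid.** A free intercept plus an arm-by-time term has the right size under the null. A reader might infer a biased or wrong test, and the documents do not support that. This stands.
- **The article does not fix the details.** It says slope, not linear slope, and does not name the tested contrast. Both may be settled in an analysis plan that is not shown. A month-24 difference read from the same free-baseline model would have about 72% to 75% power for the constant effect at ρ of .1 to .3. This stands as a limit on the slope figures. The free baseline difference, however, is stated outright.
- **The correlation range is borrowed.** It is given for viral suppression. At higher correlations the loss is small, and with an assumed random-slope variance of 0.3 the factor falls to 1.18 and 1.07 at ρ of .5 and .7. Several secondary outcomes are binary, ordinal or counts, where Gaussian ratios only indicate the direction and rough size. This stands.
- **A delayed, accumulating effect is plausible.** Unsuppressed participants can step up again at later visits. A reader might infer that the months 8–24 average is simply the better test. The last part of the working shows otherwise: for steady growth from month 4 the protocol's own slope test has 88% and 96% at ρ of .3 and .5, against 80% for the average.
- **The different target from the primary outcome is explained.** The article gives its reason, and no power is claimed for secondary outcomes. That difference alone is therefore no contradiction.

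**Conclusion.** The point holds as an avoidable loss of precision on secondary outcomes. Leaving the baseline arm difference free multiplies the variance of a linear slope difference by 1.56 to 2.27 over the protocol's correlation range, and by 1.13 to 1.28 at assumed correlations of .5 to .7. These factors rest on compound symmetry, seven complete visits, a continuous outcome and a linear reading of slope. The common-baseline constraint gained precision in every case checked. The choice between slope and months 8–24 average is a trade-off that depends on how the effect develops. The primary analysis is untouched and nothing here is an error in the test.

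**What to change.** In Data Analyses, Aim 1, replace the free baseline difference for secondary outcomes with a common baseline mean across arms (a constrained longitudinal model). Alternatively, adjust for the baseline value and keep only post-baseline visits as outcomes. Do this whichever post-baseline contrast is tested, and name that contrast.

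As an option, because the arms share the same care until the month-4 result, also report the average arm difference over months 8 to 24, the visits used in Sample Size Calculations. State whether the arms are held equal at month 4 or left free there. Present this average beside the slope difference and do not describe it as uniformly more powerful.

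The cost is a change of wording, with the same data and visits. Treating visit as categorical for the optional average adds a few parameters.

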### Outcome Measures

#### Primary Outcome: HIV Viral load

The primary outcome measure is a suppressed viral load at each 4-month assessment for 24 months. At both sites, whole blood is collected with the anticoagulant EDTA and sent at ambient temperature to an internal laboratory where plasma is separated. In addition, 1.5-3.0 mL plasma is shipped to an off-site CLIA-certified laboratory to measure viral load by quantitative HIV-1 RNA real time polymerase chain reaction with a level of detection of 20 copies/mL. Samples from New Orleans are measured at room temperature and those from Los Angeles are measured after they are frozen and thawed. The study team will receive the results through the laboratory’s online portal.

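### Covariates for the primary model are chosen by observed baseline imbalance, with propensity scores as needed, instead of being fixed in advance on prognostic grounds

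*Protocol article*

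**What the plan says.** The adjustment rule is in the Protocol article, Data Analyses, Aim 1. It starts from an expectation: "We anticipate that randomization will balance out sociodemographic and other important background characteristics across study arms". It then sets the trigger, "If characteristics are found to differ across study arms, they will be included as adjustment covariates in MLM", and leaves a further option open: "More sophisticated adjustment methods such as propensity scores will be implemented as needed". No candidate list, test or threshold is given, and nothing says when a propensity score becomes necessary. The model is described in the same section: "Generalized linear MLM will be fit to discrete outcomes such as the binary outcome for viral suppression". It is set up to test the arm difference averaged over follow-up, and no baseline covariate or site term is named.

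Other sections show what is available at baseline:

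- Recruitment Procedures places randomisation "after viral load results are obtained and entered, which typically takes several days", so every randomised participant has a viral load result beforehand.
- Primary Outcome: HIV Viral load describes the assay as "quantitative HIV-1 RNA real time polymerase chain reaction with a level of detection of 20 copies/mL", so the result is a number and not only a category.
- Aim 1 notes that "all participants are virally unsuppressed at baseline based on eligibility criteria". The yes/no baseline is therefore constant, but the quantitative value still varies.
- Overview of Methods and Aims names two cities. The outcome section says of the specimens: "Samples from New Orleans are measured at room temperature and those from Los Angeles are measured after they are frozen and thawed".

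**The concern.** When allocation is random, a baseline difference between arms is a chance event. A covariate is worth adjusting for because it predicts the outcome. Selecting on imbalance can leave out a strong predictor that happens to be balanced and bring in an irrelevant variable that happens to differ.

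Two things are at stake. First, the covariate set of the primary model, and even the method (multilevel model or propensity score), is settled only after the arms have been compared at baseline, by a criterion that nobody has written down. Second, a cheap gain in power is left unused in a trial planned at 80%.

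This is a rule that the article states, not a detail left to an unseen analysis plan. A plan that followed the article would inherit it.

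**Working it through.** **1. The plan's own figure.** Inputs from Sample Size Calculations: 88 analysed per arm (110 less 20%), 5 time points, compound symmetry with correlation ρ of .1 to .3, control suppression 6% to 20%, 80% power, two-sided .05.

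- Variance factor for a 5-visit mean: (1 + 4ρ)/5, which is .28 at ρ = .1 and .44 at ρ = .3.
- Effective n per arm at ρ = .3: 88/.44 = 200.
- Two-proportion formula with pooled variance at ρ = .3: detectable difference 8.5 points (control 6%) and 12.3 points (control 20%). Rounded up, this is the stated 9%-13%.
- At ρ = .1 the differences are 6.5 and 9.6 points.

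The figure reproduces without any covariate, so the stated power does not depend on the adjustment rule.

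**2. How often chance changes the model.** Assume that a difference means p < .05 and that k candidates are independent. P(at least one enters) = 1 − .95^k, which is 23%, 40%, 54% and 64% for k = 5, 10, 15 and 20. The Assessments section describes a baseline interview on background, risk behaviours, sociodemographics and eight further domains, so the pool is not small.

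**3. What fixed adjustment could add.** Let r be the correlation of the chosen covariates with a participant's mean suppression over follow-up. The documents give no value, so .2 to .4 is an assumption. Residual variance falls by r². Starting from exactly 80%, power = Φ(2.80/√(1 − r²) − 1.96), and the equivalent gain in participants is 220/(1 − r²) − 220.

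| r | variance reduction | power | equivalent extra participants |
|---|---|---|---|
| .2 | 4% | 81.6% | 9 |
| .3 | 9% | 83.6% | 22 |
| .4 | 16% | 86.4% | 42 |

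**4. How demanding the upper end is.** The between-person share of the variance of a 5-visit mean is 5ρ/(1 + 4ρ): .36 at ρ = .1 and .68 at ρ = .3. For r = .4 the covariates must explain .16/.36 = 45% or .16/.68 = 24% of between-person variance, in a sample restricted to unsuppressed youth.

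**5. What the stated rule recovers.** Simulation: 88 per arm, 5 visits, control rate 20%, true difference 12.5 points, within-person correlation about .29, ten candidate covariates of which one is prognostic, entry at p < .05 (assumed), linear models on participant means.

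| R² of the prognostic covariate | unadjusted power | imbalance rule | fixed adjustment |
|---|---|---|---|
| .12 (r about .35) | 80.6% | 80.8% | 84.6% |
| .29 (beyond the range in step 3) | 80.4% | 81.2% | 91.9% |

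At R² of .12 the rule recovers 0.2 of the 4.0 points available. The mean reported standard error is .0439 unadjusted, .0441 under the rule and .0413 with fixed adjustment.

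**6. Validity of the rule as written.** In the same simulation with no true effect, the rule rejects in 4.9%, 4.0% and 3.5% of trials at R² of about .12, .29 and .45. The estimated risk difference is unbiased.

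**7. Does the covariate set change the odds ratio?** In a random-intercept logit, a participant-level covariate independent of arm moves variance from the random intercept to the fixed part. If the covariate is normal, the arm coefficient is exactly the same parameter. In simulation with 60,000 participants and 5 visits, arm odds ratios without and with the covariate were 4.01/4.00, 4.11/4.06, 2.45/2.44 and 2.42/2.42.

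**The case against.** The best defence is that the rule does no harm by the plan's own standards. The trigger looks at baseline data and not at outcomes. Applied mechanically, it keeps type I error at or below 5%, leaves a linear risk difference unbiased, and gives no less power than the unadjusted calculation in Sample Size Calculations. What is lost is an optional gain whose size no document supports, and at r = .2 it is only 1.6 power points. The article also does not exclude viral load or site; it merely names neither. All of this stands, and it limits the weight of the point. It does not defend imbalance as a selection criterion.

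A reader might infer more than the documents support:

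- **That a data-chosen covariate set changes what is estimated.** Step 7 shows that it does not, materially, for participant-level covariates in a random-intercept logit. For 6% versus 15% suppression the marginal odds ratio is 2.76, and the random-intercept odds ratio is 3.2 at ρ = .1 and 4.7 at ρ = .3. That gap comes from the random effect, not from the choice of covariates. The link function is not stated either.
- **That the type I error is inflated.** Reporting the best of the unadjusted, imbalance-adjusted and fixed-adjusted results gave 7.1% to 8.6% in simulation, but the article describes no such choice. The risk lies in the undefined wording, not in the rule when followed.
- **That baseline viral load is the strongest predictor, or the only baseline information about the outcome.** Nothing in the article ranks predictors. Its introduction and discussion stress adherence barriers, depression and life circumstances, and the baseline interview covers many domains.
- **That specimen handling distorts the comparison.** It differs by city and not by arm, and nothing shows that it alters classification at 200 copies/mL.

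**Conclusion.** The point holds as a badly chosen rule for the primary model. Selection on observed imbalance, without a list or threshold and with propensity scores held in reserve, makes the primary analysis depend on undefined baseline comparisons and gives up nearly all the power that fixed prognostic adjustment could add. The gain forgone is about 2 to 6 power points (80% to 82%-86%, or 9 to 42 participants on 220) if the covariates correlate .2 to .4 with mean suppression. That range is an assumption, and its upper end is hard to reach because everyone enters unsuppressed. The case for site rests on there being two cities with different specimen handling; the article does not say whether randomisation was stratified by city. The trial's validity and its stated power are not in question. The change is worth making because it costs so little.

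**What to change.** Replace the trigger in Data Analyses, Aim 1, with a statement that the primary model adjusts for baseline log10 viral load and for site, whatever the observed balance. Keep imbalance-driven and propensity-score adjustment only as labelled sensitivity analyses. Report the arm effect as a model-standardised risk difference with its confidence interval, because Sample Size Calculations plans on percentage-point differences and a random-intercept coefficient is not on that scale.

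The cost is a change of wording and two extra fixed parameters. No new data are needed: viral load is already measured before randomisation and site is known. If the 200 copies/mL threshold also defines unsuppressed at screening, every baseline value lies above the assay's 20 copies/mL limit, so the logarithm needs no handling of undetectable results.
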